### Secondary outcomes

**1. 10 cm Visual Analog Scale (VAS):**
The Visual Analog Scale (VAS) is a widely used tool for measuring pain and is known for its high accuracy (ICC = 0.98). Participants will be asked to place a mark on a straight line to show how much pain they are feeling at that moment. The pain level is then measured in millimeters to quantify pain level [51–54].
**2. Neuropathy-specific quality of life questionnaire (Neuro QoL):**
The Neuro-QoL questionnaire is used to assess and monitor patients with diabetic peripheral neuropathy (DPN) both during and after treatment. It helps evaluate how DPN affects daily life, both physically and mentally**,** as well as overall quality of life**.** The questionnaire consists of 27 questions divided into six categories**,** each rated on a 5-point scale (1 = never, 5 = all the time) based on how often symptoms occur. The six categories include pain and tingling (paresthesia), changes in foot sensation and temperature, difficulty with balance while standing and walking, limitations in daily activities, emotional and physical dependence in relationships, and emotional distress**.** Additionally, two extra questions assess the overall impact of neuropathy on life [51,53].

### Ethical issues and informed consent

This study has been approved by the ethical committee of the Department of Physiotherapy and Rehabilitation at Jashore University of Science and Technology, Bangladesh (Approval No.: PTR-JUST/IRB/2025/01/222564). The Clinical Trials Registry-India has registered it (CTRI/2025/01/079801), and it will adhere to the Declaration of Helsinki and other international ethical standards. Participants will be given comprehensive information on the study's goals, methods, potential risks, and advantages prior to enrollment. They will provide written consent in either English or Bangla to ensure they fully understand. At any point, participants are free to withdraw from the research without facing any adverse effects.

### Study procedure

A thorough physical examination of each patient will be conducted by a diabetic foot surgeon and a consultant physiotherapist following the collection of demographic information and medical screening results. After recruitment, participants will be briefed on the participant information sheet, informed consent will be obtained, and they will be sent to a blinded assessor for baseline socio-demographic and clinical examination. After completing the baseline, the participants will be sent to a separate room to receive the intervention in a concealed envelope. After completing interventions, participants will be appointed to the assessor for outcome evaluation and briefed for the follow-up evaluations. During follow-up time, participants will be contacted over the phone, and an appointment will be scheduled with the blinded assessor for clinical evaluations. Participants will receive the treatment free of charge, and they will cover only the transport costs.

### Randomization procedures

DPSN patients would be selected according to the inclusion and exclusion criteria from the Nurul Islam Diabetic Center in Jashore, Bangladesh. There will be patient enrollment, and after baseline assessment, participants will be randomly allocated to either the intervention or control group using a computer-generated randomization sequence created by an independent researcher not involved in recruitment, assessment, or treatment. A simple random sampling method will be used to ensure equal distribution between groups. The investigator, who will not participate in the evaluation or interventions, will assign participants. Participants will receive all information that relates to the goals of the investigation and the approach used. Written consent in Bangla and/or English will be given to each patient. As research participants, they will be informed of their rights, and all of their personal data will be kept private.

### Blinding

This trial will be participant- and assessor-blinded. Participants will not be informed of their group allocation, as both interventions are structurally similar, thereby reducing the likelihood of identification. Outcome assessors will remain blinded to minimize assessment bias. Physiotherapists administering the treatments cannot be blinded due to the nature of the interventions but will have no role in outcome evaluation, data handling, or analysis. Allocation concealment will be ensured via a secure randomization system managed by an independent researcher uninvolved in recruitment, treatment, or assessment. To maintain blinding, participants will be instructed not to disclose their intervention during follow-up, and the effectiveness of blinding may be evaluated at study completion by querying participants and assessors about perceived group assignments.

### Data audit and management

Data will undergo two checks to ensure accuracy and will be frequently verified by an external reviewer from the Department of Mathematics at Jashore University of Science & Technology. Data will be audited in a printed questionnaire, and in Excel formats to examine redundancy, outliers, and de-identified for the data analysis process.

### Data analysis

All statistical analyses will be performed using appropriate statistical software (SPSS Statistics, version 23). Descriptive statistics will be used to summarize baseline characteristics, with continuous variables presented as mean ± standard deviation (SD) and categorical variables as frequencies and percentages. A p-value < 0.05 will be considered statistically significant, with a 95% confidence interval (CI). The Shapiro-Wilk test and graphical analysis will be used to assess whether the data are normally distributed. A repeated-measure ANOVA will be used to analyze group differences (intervention vs. control), changes over time, and the group-by-time interaction to assess treatment effects. Appropriate nonparametric tests, such as the Friedman test for within-group comparisons and the Mann–Whitney U test for between-group comparisons, will be employed if the assumptions required for parametric testing are not met. When appropriate, post hoc analyses will be carried out, and Type I error will be controlled using the Bonferroni correction. All randomized participants will be included in the analysis using an intention-to-treat (ITT) strategy, and missing data will be handled appropriately based on the last observation carried forward method.

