**Methods:**

An assessor and patient-blinded randomized clinical trial (RCT) on 90 DPSN cases through hospital-based simple random sampling. Participants will be randomly assigned equally to either the Neurodynamic approach or the Sham neurodynamic approach group by concealed allocation between April and August 2025 at the Nurul Islam Diabetic Center in Jashore, Bangladesh. The experimental group will receive the Neurodynamic approach, and the control group will receive the sham approach; however, both groups will receive transcutaneous electrical nerve stimulation (TENS) and home exercises for 12 sessions over 4 weeks. A pretest will be taken at baseline, a posttest after 4 weeks, and a follow-up evaluation after 12 weeks. In addition to outcome measures, manageable and fatal adverse events will be documented and reported.

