## Methods

### Study design

The study will be an assessor and patient-blinded Randomized Clinical Trial (RCT) at the Nurul Islam Diabetic Center in Jashore, Bangladesh. Ninety (90) patients diagnosed with DPSN by a diabetic foot surgeon and experiencing pain, burning, or tingling in the lower limbs or peripheral nerves will be randomly recruited via hospital-based simple randomization between April 2025 and August 2025. The recruited patients will be randomly allocated to either the Neurodynamic Mobilization (Experimental) (n = 45) or Sham Neurodynamic Mobilization (Control) (n = 45) groups in a 1:1 ratio using simple random sampling. The experimental group will receive Neurodynamic mobilization, and the control group will receive Sham Neurodynamic Mobilization for 12 sessions in 4 weeks; both groups will receive common foot exercises and transcutaneous electrical nerve stimulation (TENS) as a common treatment. The post-test will be taken 4 weeks after baseline assessment and recruitment, and the follow-up will be taken 12 weeks after the post-test. The follow-up assessment of the last recruited participant will end by August 2025. The study protocol will follow the Fig 1. SPIRIT (Standard Protocol Items: Recommendations for Interventional Trials) guideline of the study protocol, ensuring a clear and comprehensive study design, including participant recruitment, randomization, intervention allocation, and follow-up assessments.. The results will be reported in accordance with the CONSORT (Consolidated Standards of Reporting Trials) flow diagram (Fig 2) of participant progression, which shows the flow of participants through the enrollment, allocation, follow-up, and analysis phases of the randomized clinical trial.

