### Sample size calculation

The number of patients was determined using G*Power (version 3.1.9.7) based on changes in neuropathic pain scores from a study by [29], which examined the effect of the Michigan Diabetic Neuropathy Score (MDNS), a validated tool used to assess the severity of diabetic peripheral neuropathy. 42 subjects per group were shown to be necessary based on an effect size of 0.62, an alpha level of 0.05, and a power of 0.8. Hence, the total sample size was 84. [30]. We anticipate a 10% dropout rate, so we will recruit 90 participants in total and allocate them equally between the two groups.

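### The repeated-measures ANOVA leaves open which effect, at which time, is the confirmatory test of MDNS, and one candidate, the group main effect, is diluted by the baseline

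*Protocol article*

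**What the plan says.** The Data analysis section gives the method in one sentence: "A repeated-measure ANOVA will be used to analyze group differences (intervention vs. control), changes over time, and the group-by-time interaction to assess treatment effects". The threshold is general: "A p-value < 0.05 will be considered statistically significant". Multiplicity appears once: "When appropriate, post hoc analyses will be carried out, and Type I error will be controlled using the Bonferroni correction". If parametric assumptions fail, the section turns to alternatives "such as the Friedman test for within-group comparisons and the Mann–Whitney U test for between-group comparisons". In this section baseline is mentioned only for descriptive summaries, and missing values are filled by last observation carried forward.

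The Outcome measures section names MDNS as primary without a time point. The Abstract gives three assessments: "A pretest will be taken at baseline, a posttest after 4 weeks, and a follow-up evaluation after 12 weeks". The Study design section times the last one differently: "the follow-up will be taken 12 weeks after the post-test".

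The Sample size calculation states that "42 subjects per group were shown to be necessary based on an effect size of 0.62", with alpha 0.05 and power 0.8, and says the calculation rests on changes in scores.

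**The concern.** A repeated-measures ANOVA with two arms and three occasions produces several F-tests, and two of them bear on treatment. They answer different questions.

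- **Group main effect.** This compares the arms on the average of all occasions in the outcome vector. If baseline is one of them, randomisation makes the expected difference there zero, so the average understates the effect after treatment.
- **Group-by-time interaction.** With three occasions this has 2 degrees of freedom. It shows that the arms' profiles differ somewhere, but not when, by how much, or in which direction at a given visit.

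The protocol lists both without ranking them. One can be significant when the other is not, and nothing says which result decides the trial. The choice could then be made after the data are seen. The sample size also appears to belong to a third test, a plain comparison of two means.

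**Working it through.** **Inputs from the protocol.** Effect size 0.62, alpha 0.05, power 0.80, 42 per group, three occasions.

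**Assumptions.** The protocol gives no correlation r between occasions, so r = 0.3, 0.5, 0.7 and 0.8 are shown. Equal variances (SD = 1) and equal correlations are assumed. The 0.62 is taken as a raw between-arm difference in SD units at one time.

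**Step 1: the plan's own figure.** A two-sided two-sample t-test with d = 0.62, alpha 0.05 and power 0.80 needs 41.8, so 42 per group (power at 42: 0.802). The one-sided version needs 33. The stated 42 therefore reproduces as a two-sided comparison of two means.

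**Step 2: is baseline a level of time?** The text does not say so. The ANOVA is to examine change over time, there are three assessments, and the within-group fallback is the Friedman test, which is meant for three or more related occasions. Only two assessments are post-baseline. No baseline covariate is mentioned. Baseline as a level is the natural reading.

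**Step 3: dilution of the group main effect.**
- Sustained effect: (0 + 0.62 + 0.62)/3 = 0.41 SD.
- Effect halved by follow-up: (0 + 0.62 + 0.31)/3 = 0.31 SD. The true post-baseline average is (0.62 + 0.31)/2 = 0.465, so dilution accounts for 0.465 to 0.31; the rest of the gap from 0.62 is the assumed decay.

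The SD of a three-occasion mean is √((1 + 2r)/3). The noncentrality is the diluted effect divided by this SD, times √(42/2). For the sustained effect at r = 0.5: 0.413/0.816 × √21 = 2.32, which gives 63% power on 82 df.

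**Step 4: interaction.** Noncentral F on 2 and 164 df, with λ = (42/2) × Σ(δ − mean δ)²/(1 − r). For the sustained effect at r = 0.5, Σ = 0.2563 and λ = 21 × 0.2563/0.5 = 10.76, which gives 84%.

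**Step 5: baseline-adjusted week-4 contrast.** The residual SD is √(1 − r²). At r = 0.5: 0.62/0.866 × √21 = 3.28, which gives 90%.

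Power at 42 per arm:

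| Test | r = 0.3 | 0.5 | 0.7 | 0.8 |
|---|---|---|---|---|
| Group main effect, sustained | 73% | 63% | 55% | 52% |
| Interaction, sustained | 69% | 84% | 97% | >99% |
| Interaction, halved by follow-up | 56% | 71% | 91% | 98% |
| Adjusted week-4 contrast | 84% | 90% | 98% | >99% |

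Simulation with 20,000 trials per setting agrees to within about one percentage point.

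**Step 6: type I error.** Each test alone holds about 5%. If a positive result on either the group effect or the interaction may be claimed, the rate is 1 − 0.95² = 9.75%; simulation gave 9.6% to 10.2%.

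**Step 7: sensitivity to the meaning of 0.62.** If 0.62 is standardised on the SD of change, the raw effect is 0.62 × √(2(1 − r)). The factor (1 − r) then cancels from λ, and interaction power is 84% (sustained) or 71% (halved) at every r. The group main effect is still cut to two thirds.

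**The case against.** The strongest reply is that, in a baseline, post-test and follow-up ANOVA, the interaction is the usual treatment test, and the closing words about assessing treatment effects can be read as attaching to it alone. On that reading type I error is 5%, and dilution of the main effect does not touch the decisive test. The interaction is valid without baseline adjustment in a randomised trial, and for a sustained effect it reaches 80% power once r is about 0.5 or more. This stands. But the sentence does not say it, and a 2-df interaction still gives no estimate at a named visit.

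Two stronger readings are tempting, and the document supports neither. A reader might infer that the false-positive rate doubles. That needs a rule that success on either effect counts, and no such rule is stated; 9.75% is the figure only if either may be claimed. A reader might also infer that the planned 80% power is out of reach for every listed test. The interaction figures above contradict that.

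It can also be said that the ranking of effects and the choice of covariates are commonly left to a statistical analysis plan, and that time-specific contrasts could appear among the Bonferroni-corrected post hoc analyses. Silence alone would therefore be no finding. The point rests on what the article does state: a named method, with its effects listed side by side, one of which is a poor measure of treatment benefit.

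**Conclusion.** The concern holds in limited form. The protocol does not fix which ANOVA effect, at which time, is the confirmatory test of MDNS. If baseline is a level of time, which is a strong inference rather than stated text, the group main effect estimates two thirds of a sustained effect and has 52% to 73% power instead of 80%. The interaction avoids that dilution, but falls short of 80% at r = 0.3, and also at r = 0.5 if the effect halves by follow-up. Type I error lies between 5% (interaction only) and about 9.75% (either effect).

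The power figures rest on assumed correlations and on 0.62 being a raw difference at one time. That reading reproduces the 42 per group, but the sample-size text speaks of changes in scores. The dilution factor and the lack of a named confirmatory test depend on neither assumption.

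**What to change.** Before unblinding, name one confirmatory contrast: the between-arm difference in MDNS at the week-4 post-test, adjusted for baseline MDNS, reported with its 95% CI and tested at two-sided 0.05. Take it from an ANCOVA, or from a mixed model of the two post-baseline values with baseline MDNS as covariate and terms for arm, visit and arm-by-visit. Report the follow-up contrast as secondary. Do not use the group main effect with baseline in the outcome vector.

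Two other passages must follow. The last-observation-carried-forward rule has to be aligned with the chosen model, since a mixed model uses the observed values without filling them in. The follow-up timing in the Abstract and in Study design must be reconciled so that the secondary contrast has a defined time.

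No new data or software is needed: baseline MDNS is already collected and SPSS fits both models. The cost is that one time point must be declared primary, so a benefit that appears only at follow-up would count as secondary evidence.

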One of the key findings of this study will be the improvement in the Michigan Diabetic Neuropathy Score (MDNS) among participants in the experimental group. The reduction in MDNS scores will suggest that neurodynamic mobilization positively impacts nerve function and reduces sensory disturbances. On the other hand, improvements in the Visual Analog Scale (VAS) scores will indicate that participants experienced less pain after receiving the intervention. This will be important because chronic pain is a major concern for individuals with DPN, affecting their daily activities and quality of life [55,56]. Another significant outcome of this study will be the improvement in Neuropathy-Specific Quality of Life (Neuro-QoL) scores**.** Participants in the experimental group reported better physical function, reduced pain-related limitations, and improved overall well-being [45–50]. This suggests that neurodynamic mobilization, along with foot exercises, may enhance daily functioning and reduce the risk of further complications, such as falls and foot ulcers [11,12]. Possible explanations for these improvements are that neurodynamic mobilization promotes nerve gliding and reduces mechanical stress on nerves, which will help restore normal nerve function. The techniques used in this study will target key nerves affected in DPSN, including the sciatic, tibial, sural, and common peroneal nerves. By enhancing nerve mobility, the intervention may have improved sensory and motor function in the lower limbs [54,57,58]. The inclusion of foot exercises in both groups will have also contributed to positive outcomes. These exercises will help improve sensory input, circulation, and muscle strength, which are essential for maintaining foot health in individuals with DPSN [53,54,57,58]. The control group will also show some improvement, likely due to the benefits of foot exercises and Transcutaneous Electrical Nerve Stimulation (TENS) therapy, which is known to reduce pain and improve circulation. However, the experimental group will show greater improvements, indicating that neurodynamic mobilization provides additional benefits [41–45].

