Despite these promising findings, this study will have some limitations**.** The sample size may be relatively small, and the study will be conducted at a single center, which may limit the generalizability of the results. Additionally, the long-term effects of neurodynamic mobilization were not assessed beyond the 12-week follow-up period. Future studies should include larger sample sizes, multiple study centers, and longer follow-up periods to determine whether the benefits of neurodynamic mobilization are sustained over time [52–54,57,58].

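### The only stated missing-data rule is LOCF, which enters the week-4 score as follow-up, or baseline as week 4, for participants who miss a visit

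*Protocol article*

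**What the plan says.** The Data analysis section sets the analysis population, the model and the missing-data rule together:

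- Population: "All randomized participants will be included in the analysis using an intention-to-treat (ITT) strategy".
- Model: "A repeated-measure ANOVA will be used to analyze group differences (intervention vs. control), changes over time, and the group-by-time interaction".
- Missing data: "missing data will be handled appropriately based on the last observation carried forward method".

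No other missing-data method and no sensitivity analysis is named.

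The visit schedule determines what LOCF does here. Treatment ends at week 4; for the control arm, "the control group will receive Sham Neurodynamic Mobilization for 12 sessions in 4 weeks", and the experimental arm has the same schedule. The abstract states: "A pretest will be taken at baseline, a posttest after 4 weeks, and a follow-up evaluation after 12 weeks". The Study design section states that "the follow-up will be taken 12 weeks after the post-test". The second text puts follow-up at week 16. The first can be read as week 12. Follow-up is off treatment on either reading.

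The Discussion expects both arms to get better: "The control group will also show some improvement", with a larger gain in the experimental arm.

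**The concern.** With only three visits, the rule can do just two things.

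- **Seen at week 4, missing at follow-up.** The score taken at the end of a course of 12 sessions is entered as the follow-up score. It is 12 weeks old on the Study design timing, or 12 − 4 = 8 weeks old if the abstract means week 12 from baseline. The entry assumes that nothing changed after treatment stopped.
- **Lost before week 4.** Baseline is entered as the week-4 score, and also as the follow-up score if the participant does not return. The entry assumes no change, although the protocol expects improvement in both arms.

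The first can create a follow-up difference that is not there. The second dilutes a real effect when loss is equal, and works against the arm with more loss when it is not. LOCF therefore cannot be defended as conservative. In both cases the filled-in scores enter the ANOVA as measurements, so the standard errors ignore the uncertainty of the imputation. MDNS is the primary outcome and the protocol names no single primary visit, so the primary analysis is affected.

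This is a choice that the protocol states, not a detail left to an analysis plan. An analyst who follows the text will run LOCF.

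**Working it through.** **Inputs from the protocol (Sample size calculation, Study design).** Effect size 0.62, alpha 0.05, power 0.80, 42 per group; 90 recruited and split equally, so 45 per arm; anticipated dropout 10%.

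**The plan's own figure.** A two-sided two-sample t test with effect 0.62 and 42 per group has power 0.802 (41 per group gives 0.792). The 42 reproduces. Sidedness is not stated; a one-sided test would need only 33 per group by the normal approximation, so two-sided is assumed.

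**Assumptions not in the protocol.** The 0.62 SD effect is present at week 4; the correlation between visits is 0.5; loss is independent of outcome; loss rates above 10%, unequal loss and the arm-specific gains are illustrative.

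**1. Loss after week 4, equal in both arms.** Let m be the share missing at follow-up but seen at week 4, and d the true follow-up difference in SD:

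expected LOCF difference = (1 − m) × d + m × 0.62

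| m | d = 0 | d = 0.31 (half kept) | d = 0.62 (fully kept) |
|---|---|---|---|
| 10% | 0.062 | 0.341 | 0.62 |
| 20% | 0.124 | 0.372 | 0.62 |
| 30% | 0.186 | 0.403 | 0.62 |

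The bias is m × (0.62 − d). At m = 10% it is 0.062, 0.031 and 0 across the three columns.

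**2. Rejection rate when d = 0.** Simulation with 45 per arm, correlation 0.5 and an uncorrected two-sided 5% t test at follow-up gives about 6% at 10% loss, 9% at 20% and 13 to 14% at 30%.

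**3. Unequal loss after week 4.** Suppose week-4 gains of 1.12 SD (experimental) and 0.50 SD (control), which differ by 0.62, both gone by follow-up:

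spurious difference = m_E × 1.12 − m_C × 0.50

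- 20% vs 5% lost: 0.224 − 0.025 = 0.199 SD, about 14% rejection.
- 15% vs 5% lost: 0.168 − 0.025 = 0.143 SD, about 10% rejection.
- 5% vs 15% lost: 0.056 − 0.075 = −0.019 SD, so the sign reverses.

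**4. Loss before week 4 (baseline carried forward).**

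- Equal loss of 10%: 0.62 × (1 − 0.10) = 0.558 SD in place of 0.62.
- Loss of 15% in one arm and 5% in the other, with both arms improving by 1 SD: 1.0 × (0.15 − 0.05) = 0.10 SD of bias against the arm with more loss.

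**The case against.** The strongest reply is that the harm is small on the plan's own terms. The only loss figure in the protocol is 10%. With equal loss of that size, about 90% of follow-up scores are observed, the worst case in the first table is 0.06 SD, and rejection rises only from 5% to about 6%. The larger figures need more loss or unequal loss, and an effect that vanishes completely. This stands, and it limits the severity.

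The test in step 2 is also not the plan's main test. The plan uses a group-by-time ANOVA and applies Bonferroni to post hoc comparisons. If three visit-wise comparisons were corrected (an assumed number, alpha 0.05/3 = 0.0167), the rejection rates would be about 2%, 3% and 6% at 10%, 20% and 30% loss. Moreover, if a true week-4 effect exists, a significant interaction is not a false positive. Both points stand. They reduce the rejection rates but leave the bias in the follow-up estimate unchanged.

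A reader might infer that the whole follow-up analysis carries the week-4 result forward and so presupposes durability. The text does not support that: only participants who miss follow-up are affected. Nor is durability a numbered objective. It is inferred from the off-treatment visit and from the Discussion's remark that "the long-term effects of neurodynamic mobilization were not assessed beyond the 12-week follow-up period".

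None of this makes LOCF a sound main method. Its bias depends on the pattern of loss, which is unknown in advance. Loss above 10% is also plausible: the Study procedure section has participants called back by phone after treatment ends, at their own transport cost.

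**Conclusion.** The point holds in a limited form. The protocol fixes LOCF as its only missing-data rule. In this three-visit design that imposes persistence on participants lost after week 4 and no change on those lost earlier, and imputed scores count as observed.

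Under the stated assumptions, with no true difference at follow-up, the spurious difference is about 0.06 SD at the planned 10% equal loss and 0.12 to 0.19 SD at 20 to 30%. The corresponding uncorrected rejection rates are about 6%, and about 9 to 13%. The bias is halved if half the effect remains and is zero if all of it remains. In the assumed 20% vs 5% split it reaches 0.20 SD.

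It would go too far to say that following the plan must give a misleading result or will inflate the benefit. The size and direction depend on how much loss occurs, when, in which arm, and how far the effect fades. Severity: should be fixed, ideally before any unblinded analysis.

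**What to change.** Replace LOCF as the main method for all three outcomes (MDNS, VAS and Neuro-QoL) with a linear mixed model fitted by REML with unstructured covariance. It uses every observed score of every randomised participant, with terms for group, visit and group-by-visit.

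Handle the baseline of the same outcome in one way only:

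- as a covariate, with week 4 and follow-up as the outcome visits; or
- as an outcome visit, with the baseline means of the two arms constrained to be equal.

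Using it as both covariate and outcome visit would count it twice.

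Add one sensitivity analysis under missing not at random, such as delta-adjusted multiple imputation. LOCF may stay, but only as a further sensitivity analysis. State the follow-up time once, since the abstract and the Study design section can be read differently.

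The cost is a few sentences in the Data analysis section and a few lines of syntax; the mixed-model procedure in the named software (SPSS 23) fits the model. No visit, sample size or procedure changes. The small downside is that the main analysis relies on missing at random, which the sensitivity analysis is there to probe.
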